### **2.2 ELIGIBILITY CRITERIA**

#### **2.2.1 Inclusion Criteria**

1. Positive SARS-CoV-2 diagnostic (on pharyngeal swab of deep airways material)
2. Positive pressure ventilation (either non-invasive or invasive) from > 24 hours
3. Invasive mechanical ventilation from < 96 hours
4. P/F ratio  $\leq 150$
5. D-dimer level  $\geq 6$  x upper limit of local reference range
6. PCR  $\geq 6$  fold\_upper limit of local reference range

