### **2.4.2 Secondary Endpoints:**

- Ventilation free days (VFDs) at day 28, defined as the total number of days that patient is alive and free of ventilation between randomisation and day 28 (censored at hospital discharge). Ventilation is considered as positive pressure ventilation, either invasive or non-invasive. Periods of assisted breathing lasting less than 24 hours for surgical procedures will not count against the ventilation free days calculation;
- Need of rescue administration of high-dose steroids or immune-modulatory drugs;
- Occurrence of switch from non-invasive to invasive mechanical ventilation during ICU-stay;
- Delay from start of non-invasive ventilation to switch to invasive ventilation;
- All-cause mortality at ICU discharge and hospital discharge;
- ICU free days (IFDs) at day 28, defined as the total number of days between ICU discharge and day 28. If death occurs during the ICU stay before day 28 the ICU free days calculation will be 0. The ICU readmission before day 28 after randomization will be considered;
- Occurrence of new infections from randomization to day 28; including infections by Candida, Aspergillus, Adenovirus, Herpes Virus e Citomegalovirus
- Occurrence of new organ dysfunction and grade of dysfunction during ICU stay. Organ dysfunction is defined as a Sequential Organ Failure Assessment (SOFA) score  $\geq 3$  occurring after randomization, grade of dysfunction is measured with SOFA score (see SOFA score in APPENDIX 4) daily from randomization to ICU discharge (censored at day 28);
- Objectively confirmed venous thromboembolism, stroke or myocardial infarction;
- Occurrence of major bleeding (safety end point), defined as transfusion of 2 or more units of packed red blood cells in a day, bleeding that occurs in at least one of the following critical sites [intracranial, intraspinal, intraocular (within the corpus of the eye; thus, a conjunctival bleed is not an intraocular bleed), pericardial, intra-articular, intramuscular with compartment syndrome, or retroperitoneal], bleeding that necessitates surgical intervention and bleeding that is fatal (defined as a bleeding event that was the primary cause of death or contributed directly to death);

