### **2.4.3 Physiological and Processes of care outcomes**

- Vital signs such as mean arterial pressure (MAP), heart rate (HR), respiratory rate (RR), diuresis and systemic body temperature and fluid balance will be recorded daily from inclusion until ICU discharge (censored day 28);
- Routine laboratory test parameters for organ function assessment: haemoglobin, platelets count, white blood cells count, troponin, coagulative parameters (INR, PT, aPTT), parameters for liver (AST, ALT, bilirubin) and renal function (creatinine) will be recorded daily from inclusion to ICU discharge (censored at day 28);
- Blood cells count, C-reactive protein (CRP), procalcitonin (PCT) and interleukin 6 (IL-6) will be recorded daily from inclusion to ICU discharge (censored at day 28);
- Ventilation mode, inspired oxygen fraction and arterial blood gas analysis parameters will be recorded daily from inclusion to ICU discharge from (censored at day 28);
- Adjunctive treatment such as pronation cycles, Nitric Oxide or ECMO will be recorded daily from inclusion to ICU discharge from (censored at day 28);
- New blood, respiratory and urinary-tract infections will be recorded from randomization to day 28;
- Viral reactivation measured by CMV DNA titres will be recorded from randomization to day 28;
- Need of new renal replacement therapy (intermittent haemodialysis or continuous veno-venous hemofiltration) from randomization to 28 days.

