| Liver
(Bilirubin; mg/dl)                                               | <1,1                                | 1,2 - 1,9                            | 2,0 - 5,9                                                    | 6,0 – 11,9                                                                             | >12                                                                                   |
| Renal
(Creatinine; mg/dl
/diuresis ;ml/24h)                         | <1,1
+
diuresis >
500      | 1,2 - 1,9
+
diuresis >
500  | 2,0 - 3,4
+
diuresis >
500                          | 3,5 – 4,9
o
diuresis
<500                                                     | >5
o
diuresis
<200                                                           |

A - Values are with respiratory support.

B – Catecholamines are specified as follow:

|        |                |
|--------|----------------|
| Dop    | Dopamine       |
| Dob    | Dobutamine     |
| Epi    | Epinephrine    |
| Norepi | Norepinephrine |

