- Routine laboratory test parameters for organ function assessment: haemoglobin, platelets count, white blood cells count, troponin, coagulative parameters (INR, PT, aPTT), parameters for liver (AST, ALT, bilirubin) and renal function (creatinine) will be recorded daily from inclusion to day 7 and then at day 14, 21, 28, censored at ICU discharge;
- Blood cells count, C-reactive protein (CRP) and procalcitonin (PCT), IL-6, immunoglobulins titers (IgG, IgA, IgM) will be recorded daily from inclusion to day 7 and then at day 14, 21 and 28, censored at ICU discharge;
- Beta-D Glucan in the blood and/or Galactomannan in the BAL will be recorded at admission and then every 3-5 days, censored at ICU discharge
- Ventilation mode (spontaneous breathing or mechanical ventilation), inspired oxygen fraction and arterial blood gas analysis parameters will be recorded daily from inclusion to ICU discharge, censored at day 28;
  - Adjunctive treatment such as pronation cycles, Nitric Oxide or ECMO will be recorded daily from inclusion to ICU discharge from (censored at day 28);
- New blood, respiratory and urinary-tract infections and the implicated microorganisms will be recorded from randomization to day 28;
- Viral reactivation measured by ADENOVIRUS, HSV e CMV DNA titres will be recorded from randomization to day 28, censored at ICU discharge;
- Need of renal replacement therapy: from randomization to 28 days, censored at ICU discharge.

D) Primary Outcome:

- All-cause mortality will be measured at day 28.

E) Secondary Outcomes:

- All-cause mortality will be measured at ICU discharge and hospital discharge
- SOFA score and its components will be recorded daily from randomization to ICU discharge (censored at day 28);
- Ventilation free days (VFDs) at day 28, measured at day 28;
- ICU free days (IFDs) at day 28, measured at day 28;
- Need of rescue administration of high-dose steroids or immune-modulatory drugs, measured from randomization to ICU discharge, censored at day 28;
- Switch from non-invasive to invasive mechanical ventilation from randomization to ICU discharge, censored at day 28;
- Occurrence of new infections will be recorded from randomization to day 28;
- Occurrence of objectively confirmed venous thromboembolism, stroke or myocardial infarction will be recorded from randomization to day 28;
- Occurrence of protocol related adverse events (see chapter 5.2) at day 28 (safety endpoint).

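### The new-organ-dysfunction endpoint (SOFA ≥3) names neither total nor component and sets no baseline rule, although every eligible patient already scores ≥3 at entry; the grading table and laboratory schedule behind it also need correction

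*Protocol*

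**What the plan says.** Section 2.4.2 lists as a secondary endpoint "Occurrence of new organ dysfunction and grade of dysfunction during ICU stay". The event is then defined: "Organ dysfunction is defined as a Sequential Organ Failure Assessment (SOFA) score" of 3 or more, "occurring after randomization, grade of dysfunction is measured with SOFA score (see SOFA score in APPENDIX 4) daily from randomization to ICU discharge", with censoring at day 28. The bullet mentions neither total nor component score, and no baseline value.

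Four other places bear on it:

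- **Section 2.2.1** requires "Positive pressure ventilation (either non-invasive or invasive) from > 24 hours" and a P/F ratio of at most 150.
- **Appendix 3** holds the SOFA table, although section 2.4.2 sends the reader to Appendix 4 for it. In the respiratory row, the columns for 3 and for 4 both read ≤200, with the footnote "A - Values are with respiratory support".
- **Section 2.4.3** says of the routine laboratory tests, which include platelets, bilirubin and creatinine, that they "will be recorded daily from inclusion to ICU discharge (censored at day 28").
- **Appendix 4, item C** says of the same tests that they "will be recorded daily from inclusion to day 7 and then at day 14, 21, 28, censored at ICU discharge". Item E of the same appendix wants SOFA and its components every day until ICU discharge, up to day 28. Section 4.1 tells sites to record according to Appendix 4.

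**The concern.** An occurrence endpoint carries information only if patients can be free of the event at baseline and acquire it later. Here the threshold coincides with a state that the entry criteria impose. Depending on how an analyst fills the gap, the same data could give an event rate near 100%, exactly 0%, or something in between. The trial is open-label, so choosing among these readings once data have accrued is a real risk to the credibility of the result.

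The grade of dysfunction is the second half of the endpoint. It depends on a table that separates the grades and on having the components on the days to be scored. Both are in doubt as printed. This is a secondary endpoint, so what is at stake is the trial's evidence on organ protection or harm, not its main conclusion.

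**Working it through.** **Plan's own figure.** The endpoint has no sizing of its own; the only design figure is N=210 for 28-day mortality (section 2.6). Inputs: 50% vs 25%, two-sided alpha 0.025, power 80%. With pooled variance under the null,

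n = [z(0.9875)·√(2·0.375·0.625) + z(0.80)·√(0.50·0.50 + 0.25·0.75)]² / 0.25²
= [2.241·0.685 + 0.842·0.661]² / 0.0625 ≈ 70 per arm, and 3 × 70 = 210.

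The figure reproduces and nothing below touches it.

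**Step 1: SOFA at entry.** Section 2.2.1 gives P/F ≤150 on positive pressure ventilation. Since 150 < 200, every permitted value satisfies the Appendix 3 condition for at least 3 respiratory points. The other five components are ≥0, so total SOFA ≥3. Hence 100% of eligible patients are at or above the threshold at entry. This needs only the column for 3, not the doubtful column for 4.

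**Step 2: what each reading yields.**

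| Reading of ≥3 after randomisation | Result |
|---|---|
| Total score, or any component; any later value counts | about 100% in every arm |
| Same, but a first crossing from <3 is required | 0% in every arm |
| Per organ: component ≥3 later, <3 at baseline | five non-respiratory organs can give events; arms can differ |

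The third reading is workable. For example, section 2.2.2 excludes platelets below 100,000/mm³, so coagulation is at most 2 at entry and can become a new 3 (≤50 in Appendix 3). For illustration only, power at 70 per arm and two-sided 0.025, with assumed event rates, is 0.45 for 30% vs 15%, 0.64 for 40% vs 20% and 0.57 for 50% vs 30%.

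**Step 3: grading.** Any P/F ≤200 on support meets the columns for both 3 and 4, so these two grades cannot be told apart. Grades 0, 1 and 2 have distinct cuts (>400, ≤400, ≤300).

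**Step 4: laboratory days under Appendix 4 item C**, for a patient in the ICU to day 28.

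- Scheduled: days 0–7 (8 days) plus 14, 21 and 28 = 11 of the 29 days 0–28 (38%).
- Not scheduled: 29 − 11 = 18 days (8–13, 15–20, 22–27).
- From day 8 on: 3 of 21 days (14%).

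Under section 2.4.3 all ICU days are covered. The two schedules cannot both hold, and item C also conflicts with item E in the same appendix.

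**The case against.** The strongest reply is that the bullet speaks of new organ dysfunction and that each organ in Appendix 3 is scored 0 to 4, so ≥3 reads naturally as an organ-level threshold. Section 4.2.1 mentions single-organ SOFA, and section 4.1 and Appendix 4 item E mention the components. On that reading an organ already at ≥3 is not new and the endpoint works. A separate analysis plan might also spell out the baseline rule. It stands that this reading is available and sensible. But the protocol does not state it: section 4.2.1 refers to single organs only at admission. Section 2.4.2 sets out to define the event, so an ambiguous definition there is more than a detail left for later.

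A reader might go further and infer that the endpoint cannot separate the arms at all, that no enrolled patient can be graded, or that daily SOFA cannot be scored. The documents do not support these readings:

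- The per-organ reading can discriminate, and the daily grade keeps information whatever the threshold.
- The duplicated cut blurs only respiratory 3 versus 4. The other organs, and a patient whose P/F rises above 200, can be graded. The cell may also be an error of text extraction.
- Daily laboratory values exist if section 2.4.3 governs. Even under item C, days 0–7, 14, 21 and 28 are covered, and renal 3 or 4 can be reached from diuresis, which is recorded daily in both places. It would be too strong to say that three of the six components are simply missing.

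**Conclusion.** The concern holds in a limited form. The definition is ambiguous, and on its literal total-score or any-component reading it is met by 100% of eligible patients at entry. The occurrence endpoint is then about 100%, or 0% with a first-crossing rule, in every arm. Only the unstated per-organ reading can separate the arms. Respiratory grades 3 and 4 are indistinguishable as printed, subject to a check of the source table. The laboratory schedules contradict each other on up to 18 of days 0–28.

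This rests on three assumptions: that non-invasive positive pressure ventilation counts as respiratory support under the Appendix 3 footnote; that the entry P/F is the one used for the baseline score; and, for the day counts, that the patient stays in the ICU to day 28. The rate is about 100%, not exactly so, because a patient could improve before the first score after randomisation. The primary endpoint and the sample size are unaffected.

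**What to change.** 1. In section 2.4.2, define the event as a component score ≥3 after randomisation in an organ whose baseline component was <3. The respiratory component then cannot count as new and is described by its daily grade.
2. Check the duplicated respiratory cut in Appendix 3 against the cited SOFA source and correct it if it is in the original.
3. Point section 2.4.2 to Appendix 3 for the score.
4. Reconcile the laboratory schedule between section 2.4.3 and Appendix 4 items C and E, so that the components are collected on every day on which SOFA is to be scored.

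The cost is wording in three places and an eCRF check. If the daily schedule is kept, sites enter more routine laboratory values.

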- Occurrence of clinically relevant non-major bleeding (safety end point) defined as acute clinically overt bleeding that does not meet the criteria for major and consists of any bleeding compromising hemodynamics; spontaneous hematoma larger than 25 cm^2, or 100 cm^2, intramuscular hematoma documented by ultrasonography, haematuria that was macroscopic and was spontaneous or lasted for more than 24 hours after invasive procedures; haemoptysis, hematemesis or spontaneous rectal bleeding requiring endoscopy or other medical intervention or any other bleeding requiring temporary cessation of a study drug.

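### The transfusion criterion for major bleeding does not require any bleeding, so non-bleeding transfusions can be counted in this safety endpoint

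*Protocol*

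**What the plan says.** Protocol section 2.4.2 lists two bleeding outcomes and labels each a safety endpoint.

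- **Major bleeding** has four criteria. Under the first, it is "defined as transfusion of 2 or more units of packed red blood cells in a day". The second is "bleeding that occurs in at least one of the following critical sites", followed by the list of sites. The third and fourth are "bleeding that necessitates surgical intervention and bleeding that is fatal".
- **Clinically relevant non-major bleeding** is "defined as acute clinically overt bleeding that does not meet the criteria for major", followed by a list of qualifying events. One of these is a "spontaneous hematoma larger than 25 cm" squared, immediately followed by an alternative of 100 cm squared, with no condition saying when each size applies.

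Section 2.3 gives Group 3 unfractionated heparin at therapeutic doses and Groups 1 and 2 enoxaparin at a prophylactic dose. Sections 2.3 and 3.1 state that the trial is open-label. Section 4.2.1 compares each steroid arm with the LMWH arm and uses relative risks for binary outcomes.

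**The concern.** Three of the four major-bleeding criteria are worded as bleeding events. The first is worded as a treatment. Nothing elsewhere in the protocol limits it to transfusion given for a bleed.

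The population makes this more than a drafting nicety. Section 2.2.1 enrols patients on positive pressure ventilation with a P/F ratio of 150 or below, and section 2.4.3 foresees ECMO and new renal replacement therapy. Two units in a day without overt bleeding is plausible in any arm.

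The criterion also carries real bleeds. Gastrointestinal bleeding and haemoptysis are not on the critical-site list, so unless they are fatal or need surgery they become major only through transfusion. Section 1.1.2 itself names gastrointestinal bleeding as a possible steroid harm. The criterion therefore has to stay, but it should count the right events.

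At stake is the between-arm comparison of major bleeding, above all therapeutic heparin against prophylactic LMWH. The non-major count is also affected, because it takes only bleeds that are not already major.

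**Working it through.** **Step 1. Set the criteria side by side.**

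| Criterion | Is bleeding required by the wording? |
|---|---|
| Major 1: two or more red-cell units in one day | No |
| Major 2: critical site | Yes |
| Major 3: surgical intervention | Yes |
| Major 4: fatal | Yes |
| Non-major: parent condition | Yes, acute and clinically overt |

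Two consequences follow from the wording alone.

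- A patient with no bleed who receives two units in a day meets Major 1.
- A patient with a minor overt bleed who receives two units for an unrelated reason also meets Major 1. The bleed can then no longer be non-major, because that category is "acute clinically overt bleeding that does not meet the criteria for major".

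The four major criteria are also joined by 'and', and the text does not say that any one is enough. That is surely the intent, but it should be written.

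**Step 2. Size of the dilution (illustration).** The protocol states no bleeding or transfusion rate, so there is no figure of its own to reproduce. All rates below are assumptions.

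- True major bleeding: 12% with therapeutic heparin, 4% with LMWH (relative risk 3.0, difference 8.0 points).
- b: share of the remaining patients who receive two or more units in a day for other reasons, first taken as equal in both arms.
- Observed rate q = p + (1 − p) × b. With equal b, the observed difference is the true difference × (1 − b).

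| b | Heparin arm | LMWH arm | RR | Difference |
|---|---|---|---|---|
| 0 | 12.0% | 4.0% | 3.0 | 8.0 points |
| 5% | 0.12 + 0.88 × 0.05 = 16.4% | 0.04 + 0.96 × 0.05 = 8.8% | 1.86 | 7.6 points |
| 12% | 0.12 + 0.88 × 0.12 = 22.6% | 0.04 + 0.96 × 0.12 = 15.5% | 1.45 | 7.0 points |

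In the LMWH arm, the share of counted events that are true bleeds falls to 4.0/8.8 = 45% and 4.0/15.5 = 26%.

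A second assumed pair, 9% v 3% (also a relative risk of 3.0), gives 1.73 at b = 5%, 1.43 at 10%, 1.21 at 20% and 1.13 at 30%.

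**Step 3. Unequal background.** Suppose true bleeding is 4% in both arms, and b is 12% in one arm and 5% in the other. The observed rates are 15.5% and 8.8%. The relative risk is 0.155/0.088 = 1.76 if the heparin arm has the higher b, and 0.088/0.155 = 0.57 if the LMWH arm does. A difference in transfusion practice alone can therefore create an apparent harm or an apparent protection.

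**Step 4. Precision in context.** Section 2.6 gives 210 patients at 1:1:1, hence 70 per arm, and a two-sided alpha of 2.5%. The normal-approximation power to detect 12% v 4% is about 31% with clean counting, 19% at b = 5% and 12% at b = 12%.

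**The case against.** **The heading implies bleeding.** The item is called major bleeding, its other criteria all say so, and the non-major definition suggests two grades of the same kind of event. A sensible investigator may apply it that way. This stands as a statement of probable intent, and it means that actual miscounting is not established. But eCRF entry at 8 centres follows the written criteria, and the written criterion has no such condition.

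**The illustration uses the most sensitive scale.** The risk difference moves only from 8.0 to 7.0 points, and even a clean definition would have about 31% power for the assumed rates. Both points stand, and it would be too strong to say that the wording hides a signal the trial would otherwise detect. The relative risk is, however, the measure the plan chose, and shared background events affect it most.

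**Equal background is assumed.** It is; Step 3 shows what happens otherwise.

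**Requiring attribution adds unblinded judgement to a criterion that is otherwise a simple count.** This stands as a real, small cost, and it is why the full transfusion count should also be reported.

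Two stronger readings are tempting and are not supported.

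- A reader might infer from section 5.2, which exempts expected complications of critical illness from adverse-event reporting, that these two endpoints are the main record of heparin harm. The same section requires suspected protocol-related events to be reported, and Appendix 4 lists protocol-related adverse events at day 28 as a safety endpoint. The protocol does not rank its safety endpoints.
- A reader might infer that the two haematoma sizes also corrupt the major-bleeding count. They appear only in the non-major definition. The 100 cm squared figure may belong to the intramuscular haematoma that follows it, or a qualifier may have been lost. If both sizes do apply to the same haematoma, the rule reduces to the smaller size and still works.

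**Conclusion.** The concern holds as a defect in an endpoint definition. As written, the first criterion for major bleeding admits transfusions without bleeding, and it can also remove minor bleeds from the non-major count. The wording itself is certain; how many patients it would affect is not.

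Under the assumed 12% v 4% and an equal background of 5% to 12%, the relative risk falls from 3.0 to between 1.9 and 1.5, while the absolute difference shrinks by at most 1 point. With unequal background the bias can go either way. None of these rates comes from the protocol, so they show direction and plausible scale only.

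The primary endpoint and the sample size of 210 are unaffected. The haematoma wording is a separate, minor clarification confined to the non-major endpoint, with no shown effect on results. Correcting the transfusion criterion should be done; it is not a reason to hold the trial.

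**What to change.** In section 2.4.2:

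1. Reword major bleeding as clinically overt bleeding that meets at least one of: two or more units of packed red cells in a day given for that bleeding; a listed critical site; need for surgical intervention; fatal outcome. This ties the first criterion to a bleed and makes clear that any one criterion suffices.
2. Report all patients who receive two or more units in a day, by arm and whatever the reason, as a sensitivity count beside the endpoint.
3. In the non-major definition, give one haematoma size or state the circumstance to which each size applies.

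The cost is a wording change and one eCRF item recording whether the transfusion was for overt bleeding. The downside is that attribution rests with physicians who know the allocation; the sensitivity count shows whether the conclusion depends on it. No treatment, sample size or primary analysis changes.
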